## 2 Method and material

### 2.1 Participants and study setting

Subjects eligible for this study are patients who suffer from EDS because of untreated OSA and those meeting the inclusion/exclusion criteria listed later to ensure the generalizability of the study and minimize the influence of other contributors to EDS. The study will take place at Zealand University Hospital, Denmark. Study subjects will not receive any compensation for their participation.

### 2.2 Intervention

The clinical intervention in this study is the start of treatment with nocturnal continuous positive airway pressure (CPAP). CPAP treatment is the gold standard for moderate and severe OSA treatment and works by opening the upper airway through increased upper airway pressure. CPAP compliance has typically been set at least 4 h each night, 70% of nights, even though this line is arbitrary. CPAP is very effective at reducing Apnea-Hypopnea Index (AHI) scores but has not shown an effect in randomized placebo-controlled trials on endpoints like new cardiovascular events. However, for the effect of CPAP on EDS reduction, a “dose-dependent” effect is described in two studies (Weaver et al., 2007; Antic et al., 2011).

Assessing ULT-EEG in the 6 weeks leading up to CPAP initiation as well as for 6 weeks on treatment gives us the opportunity to compare a treatment-naïve state with a period on treatment, thereby determining the effect of CPAP on ULT-EEG and EMA-assessed sleepiness metrics. Previous studies on patients with severe OSA and baseline ESS scores above 10 have found CPAP treatment to reduce the ESS score by 4.75 points (Patel et al., 2003). Within 6 weeks of CPAP treatment, we expect to see an initial and partial sleep rehabilitation effect, as other studies have found that sleep remained disturbed as assessed by continuous actigraphy 3 months after CPAP initiation (Tippin et al., 2016).

### 2.3 EEG recording device for ultra-long-term EEG recordings

The ultra-long-term (>2 weeks) EEG recordings will be made using the 24/7 EEG™ SubQ, a Conformité Européenne (CE)-approved device manufactured by UNEEG™ Medical A/S, [name]. See Figure 2 for an image of the implant, recorder, introducing needle, and the device setup for the subjects. The system is a two-channel EEG recorder device (Viana et al., 2021) and has mostly been utilized in long-term epilepsy monitoring (Grewe et al., 2020). By double-tapping the button on the recorder, the participant can record an event in the EEG signal suitable for subjective attack registration. In experienced hands, the implantation or explantation of the device can be performed in 15 min, and the device is well tolerated by most people (Djurhuus et al., 2023). Recently, its utility in ultra-long-term sleep determination has been documented (Ahrens et al., 2023, 2024a), and stable signal quality in the ultra-long-term perspective (weeks) for spectral analysis, thereby making study design containing intervention possible (Viana et al., 2021). Despite the limited spatial resolution of two EEG channels, Gangsted et al. reached a sensitivity of 94.8% and a specificity of 96.6% using the device to detect sleep vs. wake in patients with epilepsy (Gangstad et al., 2019). See Figure 3 for an example of EEG signals recorded by the SubQ device resembling wakefulness, non-Rapid eye movement (non-REM) sleep stage 2, and non-REM sleep stage 3.

**Figure 2 F2:**
[figure not shown]
**(A)** Implant. **(B)** Recorder. **(C)** Introducing needle with mounted implant. **(D)** Implant is placed subcutaneously to collect EEG data. **(E)** External recorder attached to the skin behind the ear, placed directly above the implant housing. **(F)** Implant housing is placed subcutaneously behind the ear; lead with three electrodes is placed in the subgaleal space. **(G)** Small and discrete solution collects EEG data day and night during everyday life.

**Figure 3 F3:**
[figure not shown]
Subcutaneous EEG snippets: **(A)** Wake, **(B)** Non-REM sleep stage 2, and **(C)** Non-REM sleep stage 3.

### 2.4 Study procedures

#### 2.4.1 The implantation

The 24/7 EEG SubQ electrode will be implanted behind the ear, with the electrode positioned over the temporal lobe. The side chosen is the one the patient least sleeps on. The subjects will be instructed in mounting and using 24/7 EEG™ SubQ (according to the instruction for use) as much as possible during sleep and daytime in the study period. The subjects will be asked to create an event by double-tapping the power button on the logger when they turn off the lights and go to sleep or if they experience an episode of unintentional sleep during the day.

#### 2.4.2 PSG and MSLT

The PSG will be mounted by trained personnel on a study site and performed according to the AASM criteria for the PSG mock-up. The PSG night recordings will be made in an outpatient setting where the subjects sleep in their homes. The following day the subjects will meet on-site for the MSLT. The MSLT study protocol will follow the AASM guidelines. After that, the PSG equipment will be demounted. The PSG/MSLT recordings will be performed using CE-approved equipment. The PSG and MSLT data analysis will be conducted by a trained sleep technician according to the AASM criteria and evaluated by a physician with expertise in sleep medicine. The clinically relevant results of the PSG and MSLT will be given to the subject by a medical doctor during the following on-site visit.

#### 2.4.3 Interview

During the study period, the study subjects will be invited to participate in semistructured interviews focused on sleepiness symptoms and everyday life before and after treatment initiation.

#### 2.4.4 EMA and mobile sensing

EMA is a method for assessing patient-reported outcome measures (PROMs) in the actual situation being assessed. PROMs are always reported in a context in which the reporting might interact. In EMA studies, subjects can be tested in the context they are actually in, such as at home. EMAs are typically collected using a smartphone app installed on participants' phones. This approach has great advantages over paper and pencil, including reducing errors, avoiding “backfilling” of the sleep diary, and providing digital timestamps with exact time registrations for when the subject completed their PVT test and KSS. Furthermore, participants have been shown to have their smartphones with them at all times, including nighttime, which makes it a well-suited platform for home-based sleep studies.

This study collects subjective sleepiness scores, PVT test scores, and sleep diary data by prompting subjects to register these on their smartphones. The active collection of EMA data is supplemented with simultaneous passive mobile sensing, collecting GPS-determined location, step counts, activities detected by the phone (e.g., walking, running, and biking), screen events, battery time, and local weather data. This set of passive sensing data helps build a rich contextual picture of participants' activity levels and temperature exposure during the study. These factors are all relevant to sleepiness perception in the everyday setting. In determining sleepiness levels, it is evident that it is a situational phenomenon, and clinical variability, for instance, ESS scores, has been reported with significant day-to-day or within-day variance that was probably explained by situational sleepiness (Grewe et al., 2020).

In this study, we use the Copenhagen Research Platform (CARP) and the CARP Mobile Sensing Framework (Bardram, 2022, 2020) to collect the active EMA PROMs and the passive sensing data. CARP is an open-source research tool designed for digital phenotyping, accessible on both Android and iPhone (iOS) smartphones. In this study, data will be collected by the Technical University of Denmark (DTU) by hosting an instance of CARP and ensuring compliance with GDPR and information security. The CARP framework supports in-app consent procedures, the triggering of EMA surveys and tasks, and the automatic collection of passive sensor data.

#### 2.4.5 Subjective sleepiness and alertness

The KSS will be used to determine sleepiness levels at different times during the day. The KSS is a sleepiness rating scale from 1 (*very alert*) to 9 (*very sleepy, fighting sleep, and effort to keep awake*) We utilize the “state” dimension of the KSS in opposition to the “trait” dimension of the ESS. A 3-minute reaction-time test called the PVT test is used for alertness determination. The PVT test depicts the neurobehavioral effect of sleep loss or circadian misalignment, which is considered the gold standard. In this study, the KSS and the PVT test are EMAs, and the subjects will be prompted on their smartphone to fill these out four times a day during the 14 days before and 14 days after CPAP initiation. The specific prompting time will be at 08:00, 12:00, 16:00, and 20:00. In addition, the KSS and PVT EMAs will be available for the subject for an “at any time” registration. The subjects are instructed to take the test whenever they experience high subjective sleepiness episodes. Using this method, we bypass the global retrospective self-report necessary for filling out, for example, the ESS, which can be affected by recall bias.

#### 2.4.6 Sleep and nap diary

During the 12-week study, the participant will fill in daily “sleep and nap diary”, subjective registration of napping patterns, and sudden sleep episodes. At 08:00, the participant will receive a notification to fill in a sleep survey, asking, “What time did you get out of bed today?” and “When did you go to sleep last night?” At 21:00, the participant will receive a notification to register sleep or nap episodes that might have occurred during the day, asking, “Have you been sleeping during the day?” If yes, an additional question is posed: “How long have you been sleeping during the day?” For every daytime sleep episode, the participant is asked to determine the type of nap: “I consciously took a nap because I felt the need to”, “I fell asleep without the intention to”, and “I registered I had fallen asleep when I suddenly woke up”. The subjects are asked to press the event button of the 24/7 SubQ device one time if they experience waking up from an unintended nap during the daytime. Likewise, the subjects are asked to press the event button twice before taking a planned nap during the day. This records an event in the EEG signal.

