### 1.6 Study endpoints

• ULT-EEG is analyzed to assess potential electrophysiological biomarkers resembling sleepiness or sleep pressure, such as wake–sleep transition rate, timing, and daytime sleep patterns in the micro and macro perspective or vigilance state classification. This will be assessed through automated microsleep detection and automated sleep-stage classification methods. Using concomitant PSG and ULT-EEG, we will identify the markers of stage transition from awake to dozing/light sleep in the SubQ recording. We will do this both according to AASM criteria and in shorter segments of EEG. From this template, we will use machine learning (ML) techniques to train a classifier to detect those short transitions in the ULT-EEG recording with different levels of sensitivity and specificity.

• The correlation between ULT-EEG-derived biomarker candidates and well-known sleepiness metrics, such as the mean sleep latency and EMA collected reaction time, and ESS and KSS scores, as well as patient reports of episodes of daytime sleeping or dozing off (nap diary). From the timestamps on PVT prompts to patients, we will identify segments of interest in the ULT-EEG recording to document changes in EEG-related signs of reduced vigilance. We will use this to validate the responses on the clinical scales given by patients.

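### The published nap-diary items record no clock time and do not cover the period from the 21:00 prompt to bedtime, and the event-button coding that would link naps to the EEG is inconsistent

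*Protocol article*

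**What the plan says.** Section 2.4.6 of the protocol article describes two diary notifications a day for 12 weeks.

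- **08:00.** Two questions: when the participant got out of bed, and "When did you go to sleep last night".
- **21:00.** "At 21:00, the participant will receive a notification to register sleep or nap episodes that might have occurred during the day". A yes leads to "How long have you been sleeping during the day". Then, "For every daytime sleep episode, the participant is asked to determine the type of nap", with three options that separate a deliberate nap from two kinds of unintended sleep.

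The same section adds a device marker. Participants are to "press the event button of the 24/7 SubQ device one time if they experience waking up from an unintended nap during the daytime" and to "press the event button twice before taking a planned nap during the day". It continues: "This records an event in the EEG signal".

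Two other sections describe the button. Section 2.3 says an event is recorded by a double-tap. Section 2.4.1 asks for a double-tap at lights-off and also for an episode of unintentional daytime sleep.

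Section 1.6 names the diary among the metrics to be correlated with the EEG-derived candidates: "patient reports of episodes of daytime sleeping or dozing off (nap diary". Section 1.4 also lists it among the measures for preliminary validation. According to the abstract, the EEG is recorded around the clock for 6 weeks before and 6 weeks during CPAP.

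**The concern.** The study wants to find sleep intruding into normal waking hours, and the diary is its only daily self-report of such episodes. Two features of the printed items limit that use.

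First, the day is asked about before it has ended. The hours before bed are often quiet, and a sleepy patient may well doze then. The EEG can detect sleep in those hours, but no printed diary question asks about it. If EEG and diary are compared over all waking hours, some disagreement will come from the questionnaire and not from the marker. A change in evening dozing under CPAP would also not show in the diary.

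Second, the printed items say how long and what kind, but not when. Section 1.6 plans to use the timestamps of PVT prompts to pick out EEG segments, so the authors rely on timing elsewhere. For naps, that timing has to come from the button, and the button instructions do not agree with one another.

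**Working it through.** There is no published figure to reproduce. The check sets the data-collection rules side by side, then sizes the gap.

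**1. What covers the interval from the evening entry to bedtime?**

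| Source | Section | Covers it? |
|---|---|---|
| Nap items at 21:00 | 2.4.6 | Only up to the moment of answering |
| 08:00 survey | 2.4.6 | No; rising time and sleep time only |
| Scheduled KSS and PVT | 2.4.5 | No; last prompt at 20:00, and only in the 14 days before and 14 days after CPAP start |
| Self-initiated KSS and PVT | 2.4.5 | Possible at any time, but they record sleepiness and reaction time, not a sleep episode |
| Event button | 2.4.6, 2.4.1 | No clock limit, but worded for daytime naps |
| EEG | Abstract | Yes |

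So the EEG covers the interval and no printed diary item does.

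**2. How large is the interval?** The article gives no rising or bed times. Assume rising at 07:00, bedtime between 22:00 and 24:00, and an answer given at 21:00. The uncovered share is (bedtime − 21:00) / (bedtime − 07:00), and the diary runs 12 × 7 = 84 days.

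| Assumed bedtime | Uncovered | Waking day | Share | Over 84 days |
|---|---|---|---|---|
| 22:00 | 1 h | 15 h | 1/15 = 6.7% | 84 h |
| 23:00 | 2 h | 16 h | 2/16 = 12.5% | 168 h |
| 24:00 | 3 h | 17 h | 3/17 = 17.6% | 252 h |

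The range is about 7% to 18% of waking time per participant. Answering later than 21:00 reduces it. These are shares of time, not of dozing; the article gives no basis for the share of dozing that falls in the evening.

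**3. Can the button supply the missing clock times?**

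| Meaning | 2.3 | 2.4.1 | 2.4.6 |
|---|---|---|---|
| Any event | Double-tap | – | – |
| Lights-off | – | Double-tap | – |
| Unintended daytime sleep | – | Double-tap | One press, on waking |
| Planned nap | – | – | Two presses, beforehand |

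Taken together, a double-tap can mean lights-off, an unintended nap or a planned nap. Section 2.3 describes event recording by double-tap only, so it is unclear whether a single press is stored. Under section 2.4.6 the marker for an unintended nap gives its end and the marker for a planned nap gives its start. The marker also depends on the participant noticing the episode and remembering to press.

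**The case against.** The strongest reply has four parts.

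- **21:00 is a notification time.** No lock-out is stated, and a participant may answer later. This stands. A reader might infer that the diary closes at 21:00 or that evening dozing goes unrecorded. The article supports neither: the EEG runs around the clock, the button has no stated clock limit, and KSS and PVT can be self-initiated. What remains is that no printed diary question covers the time after the entry.
- **The button links naps to the EEG.** Section 2.4.6 says presses are written into the signal, and a press may be more precise than a recalled start time. A reader who concluded that diary episodes cannot be matched to the EEG would therefore go too far. The link exists, but its coding conflicts across three sections.
- **The diary is not an event-level reference standard.** Section 1.6 plans a correlation with the diary. The classifier template, with its levels of sensitivity and specificity, comes from simultaneous PSG and EEG, and section 1.4 validates sleep/wake classification against manually scored PSG. This stands. Turning the gap into a loss of positive predictive value would describe an analysis the article does not propose. Daily totals can serve a correlation, though a total that omits the end of the day serves it less well.
- **The article condenses the full protocol.** The app may hold a start-time field that was not printed. This is possible, since type is asked per episode. It limits how firmly the missing clock time can be asserted, but does not explain the conflicting button instructions, which are printed.

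**Conclusion.** The point holds as a limited, inexpensive improvement to a named comparator. As printed, the diary asks about daytime sleep only at the 21:00 prompt, takes no clock time, and does not ask the next morning about dozing the evening before. The uncovered period is about 7% to 18% of waking time if participants rise at 07:00, go to bed between 22:00 and 24:00 and answer at the prompt; all three are assumptions. Time-linking of diary episodes rests on button presses to which sections 2.3, 2.4.1 and 2.4.6 give conflicting meanings.

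The consequence is a weaker correlation between EEG markers and the nap diary. The article does not support the stronger conclusions that evening dozing is lost to the study, that episodes cannot be matched at all, or that detector performance is biased by a calculable amount. If the full app form already records start times and late-evening dozing, a sentence saying so settles the diary part; the button instructions would still need reconciling.

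**What to change.** 1. Add one item to the 08:00 survey: whether the participant dozed or napped between the previous evening's entry and going to bed, with the same type options as the evening diary.
2. Ask an approximate start time for each reported episode, in both surveys.
3. Until these items are live, leave the window from the evening entry to the reported time of going to sleep out of diary-EEG comparisons. Use the logged time of the entry if the app stores it, otherwise 21:00. Apply the same rule before and during CPAP.
4. Reconcile the event-button instructions in sections 2.3, 2.4.1 and 2.4.6, so that each press pattern has one meaning, and confirm which patterns the device stores. For participants already recorded, state which instruction they were given.

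The cost is a few extra seconds per participant per day and no added visits. Recalled start times will be approximate, so they are suited to finding the right stretch of EEG and not to fixing sleep onset. Step 3 gives up some evening data in the diary comparison only; the EEG from those hours stays available for every other analysis.

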### 1.4 Objectives

This project aims to develop new sleepiness biomarkers using ultra-long-term at-home EEG monitoring as a novel, new data type. We will conduct a clinical study exploring electrophysiological sleep/wake transition phenomena in a population with OSA and EDS by making ultra-long-term subcutaneous EEG recordings in subjects' real-life conditions before treatment and as they start treatment.

We follow an explorative objective and an experimental one. We aim to validate our explorative findings in an experimental setting.

Our *explorative* objective is to scrutinize subcutaneous ULT-EEG for potential biomarkers predicting sleepiness in OSA patients. Determining daytime wake-to-sleep transition rate, microsleep episodes, and macro-sleep episodes, alongside the duration and patterns of these events. In addition, vigilance determination of the odds ratio product (ORP) (Younes, 2023) or Vigilance Algorithm Leipzig (VIGALL) (Olbrich et al., 2015) can be assessed. Our explorative findings will be correlated and preliminarily validated against the well-established sleepiness metrics and questionnaires, the MSLT, the ESS, the Karolinska Sleepiness Scale (KSS), and the Psychomotor Vigilance Task (PVT) test, as well as patients' experiences of falling asleep or dozing off in the form of a “sleep and nap diary”. Any potential sleepiness biomarker derived from this study will be available for future confirmatory trials.

Our *experimental* objective is to determine the effects of CPAP treatment on sleep quality, quantity, and timing from the day-to-day perspective that ULT-EEG provides. Furthermore, the experimental design enables us to clinically validate the exploratively deduced sleepiness biomarker candidates through comparisons before and after the intervention of CPAP treatment conditions. Previous studies on CPAP's effect on reducing sleepiness have shown a dose-dependent configuration with CPAP usage. ESS scores are typically reduced by 4.75 points (Patel et al., 2003). We expect relevant biomarker candidates to follow similar patterns when CPAP is introduced in a population with severe OSA and EDS.

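### The 21:00 nap diary, as worded, takes sleep duration once per day but nap type per episode, so unintended sleep time is not identifiable on mixed-nap days and episode durations are missing on multi-nap days

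*Protocol article*

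**What the plan says.** Section 2.4.6 (Sleep and nap diary) describes the evening survey item by item. At 21:00 "the participant will receive a notification to register sleep or nap episodes that might have occurred during the day". A yes/no question comes first. "If yes, an additional question is posed": "How long have you been sleeping during the day". Then "For every daytime sleep episode, the participant is asked to determine the type of nap", with one option for a deliberate nap and two for sleep that was not planned.

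The same section adds a marker in the EEG signal. Participants are to "press the event button of the 24/7 SubQ device one time if they experience waking up from an unintended nap during the daytime" and to "press the event button twice before taking a planned nap during the day". Section 2.4.1 (The implantation) asks for a double tap at lights-out "or if they experience an episode of unintentional sleep during the day".

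The diary is one of the comparators for the EEG candidates. Section 1.4 (Objectives) describes those candidates as "Determining daytime wake-to-sleep transition rate, microsleep episodes, and macro-sleep episodes, alongside the duration and patterns of these events" and says the findings will be correlated with, and preliminarily validated against, a list of measures that includes the diary. Section 1.6 (Study endpoints) names the comparator as patients' reports of daytime sleep episodes.

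**The concern.** Duration and type are collected at different levels. The duration item refers to the day and is introduced as a single follow-up question; the type item is repeated for each episode. A day with one planned nap and one unintended doze therefore yields one sum and two labels, and the sum cannot be divided between them.

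The distinction matters in this study. The definition of EDS quoted in Section 1.1 turns on sleep that is unintentional or badly timed, whereas Section 3 treats planned napping as a way of coping. The three type options exist to separate the two, but a daily total adds them together. Separately, the EEG will produce a duration for each macro-sleep episode, and on days with several naps the diary has no duration at that level. Neither loss can be repaired once the data are collected.

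**Working it through.** No sample size, power or error rate enters this point. The check is a comparison of the items and an identifiability argument.

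**Level of each diary item (Section 2.4.6)**

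| Item | Level as worded |
|---|---|
| Slept during the day, yes/no | day |
| Duration | day, one follow-up question |
| Nap type | episode |
| Clock time of nap | not among the 21:00 items described (the 08:00 items do ask clock times, for the night) |

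**What can be recovered.** Let T be the daily total, k the number of episodes and U the unintended sleep time.

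- All episodes unintended: U = T.
- All episodes planned: U = 0.
- Types mixed: only 0 < U < T is known.
- The duration of a single episode is known from the diary only if k = 1, when it equals T.

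**Illustration (assumed values: T = 60 min, k = 2).** Both unintended: U = 60 min. Both planned: U = 0 min. One of each: U lies anywhere between 0 and 60 min. In all three cases the split of the 60 min between the two episodes is unknown.

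**How many days.** The article gives no nap frequencies, so only the dependence on assumptions can be shown. The diary runs for 12 × 7 = 84 days. Let p be the share of days with a planned nap and q the share with an unintended one. The share of mixed days is p × q if the two are independent. Without that assumption it lies between max(0, p + q − 1) and min(p, q).

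| Assumed p, q | Independent | Range without independence |
|---|---|---|
| 0.30, 0.40 | 0.12 × 84 = 10.1 days | 0 to 0.30 × 84 = 25.2 days |
| 0.50, 0.60 | 0.30 × 84 = 25.2 days | 0.10 × 84 = 8.4 to 0.50 × 84 = 42 days |

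Independence is doubtful, since planned naps may be taken precisely to avoid unintended ones. The table shows that the number could be small or large; it is not an estimate.

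**Can the event button supply the missing split?** Not reliably as described.

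- It marks one end of each nap: waking for an unintended nap, the moment beforehand for a planned one.
- The codes conflict. Under Section 2.4.6 two presses mean a planned nap and one press an unintended nap. Under Section 2.4.1 a double tap covers unintentional daytime sleep and also lights-out.
- Dividing the diary total by EEG-measured durations would be circular, because the EEG measure is what the diary is meant to check.

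**The case against.** **No named analysis needs the lost quantity.** Section 1.6 refers to reported episodes, and the diary captures those with a type for each. The phrase in Section 1.4 about duration describes what the EEG measures; most of the comparators listed there have no duration at all. This stands to the extent that the episode-based correlation is unharmed. It does not remove the point: event duration is among the explorative measures, the diary is among their comparators, and the diary does ask about duration.

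**The article may be condensing a survey that repeats the duration item.** It does not say that duration is asked only once. This stands as a reservation. However, the article quotes the items, introduces duration as one additional question about the day, and reserves the per-episode wording for type.

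**Durations recalled at 21:00 are a weak reference, especially for sleep whose onset went unnoticed.** True, but the daily total rests on the same recall, so this is no reason to prefer it.

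**Stronger readings the text does not support.** A reader might infer that unintended duration is lost on every multi-nap day; it is lost only when types are mixed. A reader might also infer that EEG durations have no diary counterpart at all; single-nap days match directly, and totals can be compared on every day. Nor does it follow that mixed days must be dropped, with an uneven loss before and after CPAP. Totals and counts by type remain usable on those days, no such exclusion is planned, and nap frequencies in either period are not given.

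**Conclusion.** The point holds within limits. If the survey works as worded, unintended sleep duration is not identifiable from the diary on days that mix planned and unintended naps, and per-episode duration agreement with the EEG is confined to single-nap days. What is weakened is a duration comparison by type or by episode, not the endpoint correlation with reported episodes.

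The size cannot be stated. On a mixed day the uncertainty spans the whole daily total, but the number of such days is unknown. The conclusion rests on the natural reading that duration is asked once per day. If the app already repeats the question for each episode, the duration problem disappears and only the wording needs correcting. The conflict between the event-button instructions remains in either case.

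**What to change.** State in Section 2.4.6 whether duration is recorded per episode. If it is not, place the duration question inside the episode loop of the 21:00 survey, next to nap type, for example: about how long did you sleep this time? Derive daily totals, overall and by type, by summing over episodes.

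Reconcile the event-button instructions in Sections 2.4.1 and 2.4.6 so that each press code has one meaning, and confirm that the recorder stores a single press as an event, since Section 2.3 describes event registration only by double tap. The marker could then help match diary episodes to EEG episodes by type.

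The cost is a small change to the app survey, one extra answer per additional nap, and a revised participant instruction. Visits and sample size do not change. The downside is a slightly longer diary on days with several naps.
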